## Methods

### Study Design (Design, Randomization, and Follow-Up)

*The Box* is a single-center open RCT, and is a parallel group study. The study will be conducted at the Leiden University Medical Center (LUMC), a tertiary care hospital in Leiden, The Netherlands. The trial is registered under clinical trial number NCT02976376 (Clinicaltrials.gov) and NL56453.058.16 (Toetsingonline.nl). After inclusion, patients will be randomized 1:1 to either *The Box* (intervention group) or to regular follow-up (control group). Block randomization per 10 participants will be performed. Randomization will be stratified per primary diagnosis (STEMI or NST-ACS) and per age (<50, 51-60, 61-70, 71-80, and >80 years). A website will be used to generate randomization lists [16].

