## Results

### Study Outcomes

The primary outcome of this study is the percentage of patients with normalized BP (defined as SBP <140 mmHg and DBP <90 mmHg), as measured at the 12-month outpatient clinic visit. Secondary outcomes of this study are detailed in Textbox 3.

Secondary outcome measures.The percentage of patients with controlled BP (defined as SBP <140 mmHg and DBP <90 mmHg), as measured at the 3-month outpatient clinic visit.Patient satisfaction, as assessed by the patient satisfaction questionnaire [18].Health care utilization, defined as an outpatient clinic visit, emergency care visit, or admission for any reason. This factor will be measured via questionnaires and verified by EMR data.Major Adverse Cardiac Events (MACEs)a. Death of any causeb. Cardiac deathc. Recurrent STEMId. Recurrent NST-ACSe. Revascularizationf. Hospitalization for heart failureg. Transient Ischemic Attackh. Ischemic strokePropensity of medication adherence, measured by the 8-item Morisky Medication Adherence Scale (MMAS-8) [21].Physical activity, as measured by the iPAQ [20].Quality of life, measured by the SF-36 [19].Percentage of patients in which a previously unknown sustained arrhythmia (>30 seconds) is detected.Cost-effectiveness, expressed as the incremental cost-effectiveness ratio.

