### Economic Analysis

To assess the cost-effectiveness of the intervention, costs per quality adjusted life year (QALY) will be calculated. The analysis will be performed from a societal perspective with a time horizon of one year. Patients will receive a health care resource use questionnaire at 6 months and 12 months. In this questionnaire, a patient will be asked to fill in their total health care utilization, such as outpatient clinic visits, emergency visits, admissions for any reason, and visits to the general practitioner. All outpatient clinic visits, emergency visits, and admissions for any reason reported in the questionnaire will be verified by EMR data. In the same questionnaire, the patient will be asked to fill in total medication use. All health care and medication use will be multiplied with standard cost prices to calculate costs [22]. To calculate indirect costs, patients will be asked to note absence from paid and unpaid work. Productivity costs will be calculated using the friction cost method. Absence will again be multiplied against standard cost prices [22]. QALYs will be calculated from utility scores from the SF-36 questionnaire, which will be administered at baseline, 1 month, 6 months, and 12 months [19,23]. Finally, costs and QALYs in both groups will be compared. It is our hypothesis that societal costs will be lower in the intervention group.

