### Statistical Analyses

A power calculation was done using R software [24], which is based on a comparison of two proportions of patients with controlled BP (defined as an SBP of 139 mmHg or less and a DBP of 89 mmHg or less). We hypothesize that in the *The Box* group, 95% of the patients will achieve controlled BP, while in the control group, 75% will achieve controlled BP [25]. For this calculation, an alpha of 0.05, a beta of 0.20, and a margin of 0.07 were chosen, yielding a sample size of 200 patients.

Data will be analyzed according to the intention-to-treat principle. Causes of missing data will be tabulated (Multimedia Appendix 1). The percentage of missing data is expected to be low. Therefore, complete case analyses will be done. Analyses will be based on the missing-at-random assumption. If the percentage of missing values exceeds 7%, multiple imputation will be applied in the analysis of the data.

After finishing the study (defined as the last patient’s last visit), the proportion of patients with controlled BP will be compared with a Chi-square test. Logistic regression might be done if serious imbalances of baseline variables exist, to correct for potential confounding variables. Percentages of patients with controlled BP at three months (secondary outcome 1), and percentages of patients in which a previously unknown sustained arrhythmia is detected, will also be compared with a Chi-square test.

Scores of questionnaires (patient satisfaction questionnaire, MMAS-8 scale, iPAQ questionnaire, and SF-36 questionnaire) and health care utilization will be compared using an independent t-test. Major Adverse Cardiac Events (MACEs) will only be reported. As the study is underpowered, no statistics will be done on MACEs. The numbers will be hypothesis-generating.

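### The primary chi-square leaves out the diagnosis and age strata used to randomise, and covariate adjustment hangs on an undefined imbalance trigger instead of being fixed in advance

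*Protocol article*

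**What the plan says.** Under Study Design, allocation is 1:1 and "Randomization will be stratified per primary diagnosis (STEMI or NST-ACS) and per age", with five age bands: under 50, 51-60, 61-70, 71-80 and over 80. The same paragraph states: "Block randomization per 10 participants will be performed".

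The primary outcome under Study Outcomes is the percentage with systolic pressure below 140 and diastolic below 90 mmHg, "as measured at the 12-month outpatient clinic visit". Statistical Analyses compares the two proportions by chi-square after the last patient's last visit. The strata do not appear in that test. The only reference to covariates is: "Logistic regression might be done if serious imbalances of baseline variables exist, to correct for potential confounding variables".

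The same section compares questionnaire scores between arms by independent t-test. For the SF-36, Economic Analysis refers to "utility scores from the SF-36 questionnaire, which will be administered at baseline, 1 month, 6 months, and 12 months". The Questionnaires section lists only three occasions: within one month, at six months and at twelve months after infarction.

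**The concern.** There are two weaknesses in what the plan fixes.

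- **The analysis does not follow the randomisation.** Stratified blocking makes the arms alike on diagnosis and age. If those factors predict blood pressure control, a test that ignores them overstates the variance of the difference and gives away some power.
- **The adjustment rule is poor as a rule.** After proper randomisation, baseline imbalance is chance, so covariates should be chosen beforehand for their prognostic value and not because they happen to differ. The sentence leaves open whether the model is fitted, what counts as serious, which variables enter, and which result governs if the two disagree. The quantity reported also changes: at the planned 95% v 75% the risk difference is 0.20, while the odds ratio is (0.95/0.05)/(0.75/0.25) = 19/3 = 6.3, and an adjusted model gives a conditional odds ratio.

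At stake is whether the primary result is uniquely determined before the data are seen, in a trial where allocation is known.

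**Working it through.** **The plan's own figure.** The plan gives no number for this point; only N = 200 enters. That total does not follow directly from the stated inputs. A two-sided two-proportion calculation gives 49 per arm, 98 in all. Subtracting the 0.07 margin, n = (0.95×0.05 + 0.75×0.25)(z_α + z_0.80)²/0.13² gives 86 per arm (172) at one-sided 0.05 and 110 per arm (220) at one-sided 0.025. This is a separate matter and does not affect what follows, so 200 is taken as given.

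**Inputs from the protocol.** 200 patients, 1:1, 2 × 5 = 10 strata, blocks of 10, planned rates 95% v 75%.

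**Assumptions not in the protocol.** A 60/40 diagnosis split; age shares of 15/27/30/20/8%; the size of the stratum effects; for the second check, 10 independent baseline covariates.

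**Step 1: ignoring the strata.** The chi-square uses the pooled variance p(1−p), where p is the overall rate. This equals the average of p_s(1−p_s) over strata s plus the variance of p_s between strata. Stratified blocking largely removes the second part from the treatment difference, so the test can only be too cautious. Results from 20,000 null trials per row (Monte Carlo error about ±0.003):

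| Stratum effect | Overall rate | Rates across strata | Chi-square | CMH |
|---|---|---|---|---|
| none | 75% | 75% | 0.052 | 0.051 |
| moderate | 75% | 57-86% | 0.049 | 0.051 |
| strong | 75% | 40-92% | 0.039 | 0.047 |
| extreme | 75% | 20-97% | 0.032 | 0.051 |
| none | 85% | 85% | 0.049 | 0.048 |
| moderate | 85% | 72-92% | 0.048 | 0.049 |
| strong | 85% | 57-96% | 0.045 | 0.051 |
| extreme | 85% | 36-99% | 0.035 | 0.049 |

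Power, chi-square v CMH, 75% control rate, 8,000 trials each:

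- Odds ratio 6.3 (95% v 75%): 0.989 v 0.987 with no stratum effect; 0.982 v 0.984 with strong effects.
- Odds ratio (0.90/0.10)/(0.75/0.25) = 3 (90% v 75%): 0.816 v 0.808 with no stratum effect; 0.775 v 0.789 with strong effects.

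**Step 2: the imbalance trigger.** Take a standardised difference |z| > 1.96 in any covariate as the trigger (assumed, since the protocol gives none). With 10 independent covariates, the chance that at least one trips it is 1 − 0.95^10 = 0.40. Results from 10,000 null trials per row (Monte Carlo error about ±0.004), with simple 1:1 allocation and equal covariate effects:

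| Log odds ratio per covariate | Triggered | Chi-square only | Follow trigger | Better of the two | Free choice |
|---|---|---|---|---|---|
| 0 | 0.392 | 0.051 | 0.052 | 0.054 | 0.063 |
| 0.3 | 0.396 | 0.047 | 0.044 | 0.052 | 0.065 |
| 0.5 | 0.403 | 0.052 | 0.046 | 0.060 | 0.078 |

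Free choice means the smallest p-value among the chi-square and models adjusting for the one, two or three most imbalanced covariates.

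**Step 3: can the fix be applied as the text stands?** Bands of under 50 and then 51-60 leave a patient aged 50 in no stratum. Under the assumed shares, the smallest cell holds 200 × 0.40 × 0.08 = 6.4 patients, so sparse strata are to be expected.

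**The case against.** The strongest reply is that the plan names one test unconditionally, the chi-square, and that the test is valid. A reader might infer from the missing strata that it is miscalibrated. The figures do not support that as a general statement: any departure from 5% is conservative, appears clearly only with strong or extreme stratum effects, and creates no false positives. No section says that diagnosis or age predicts blood pressure control. At the planned effect the power difference is negligible. All of this stands.

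A reader might also infer that the primary result will be picked after the data are seen. The text does not say so. The logistic model is optional, nothing states that it replaces the chi-square, and imbalance can be judged without looking at outcomes. Inflation needs selective reporting. The 40% chance of triggering is not an error rate. This stands too, and it limits the point to discretion left open.

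A third tempting step is to say that the SF-36 t-test wastes a baseline score. Economic Analysis names a baseline administration and a separate one at 1 month, but the Questionnaires section has only a first administration within one month. Under Patient Population, inclusion falls within 96 hours of primary PCI. A score taken before randomisation is therefore not established.

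Finally, thresholds and covariate lists are commonly left to the full plan. That is true, but the point does not rest on their absence. The article states a rule, adjustment prompted by observed imbalance, and a fuller document would have to replace that rule, not just complete it.

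**Conclusion.** The point holds in a limited form. The stated primary analysis does not reflect the stratified randomisation, and covariate adjustment is optional and prompted by the data, with nothing fixing when it applies, what it contains or which result counts.

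- **Strata:** type I error is about 3% to 4.5% if the strata strongly predict blood pressure control, and otherwise close to 5%. The power cost is 1.4 percentage points (0.775 v 0.789) for 90% v 75% with strong effects, and 0.2 points or less for 95% v 75%.
- **Trigger:** near 5% if followed mechanically (0.044 to 0.052), 0.052 to 0.060 if the better result is reported, and 0.063 to 0.078 with free choice of covariates.

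These sizes rest on assumed stratum effects, patient mix and covariates. The direction of the first does not depend on them, and the second would grow or shrink with the number of covariates on offer. This is a worthwhile and inexpensive correction, not a threat to the validity of the chi-square.

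**What to change.** 1. Name as primary the Mantel-Haenszel risk difference with its confidence interval and a Cochran-Mantel-Haenszel test, stratified by diagnosis and age group. Keep the plain chi-square as supportive.
2. Reconcile the age bands so that age 50 belongs to one stratum, and state how patients of that age were in fact allocated.
3. Fix any pooling of age bands now, not if cells turn out sparse. For example, merging over 80 with 71-80 in every case would raise the smallest merged cell, under the assumed shares, to 200 × 0.40 × 0.28 = 22.4 patients.
4. Delete the imbalance-triggered logistic regression, or label it a sensitivity analysis that cannot displace the primary result. If adjustment beyond the strata is wanted, list the covariates beforehand on prognostic grounds.
5. Reconcile the SF-36 schedules in Questionnaires and Economic Analysis. Adjust the SF-36 comparison for baseline only if a pre-randomisation score is confirmed.

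The cost is a documented change of primary test before outcomes are compared by arm, and a fixed pooling rule. Items 1 to 4 need no new data and leave N unchanged. If the strata turn out not to matter, the power given up is slight (0.808 v 0.816 at 90% v 75%).

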### Regular Follow-Up

Since 2004, the department of Cardiology of the LUMC has a dedicated care track for patients with STEMI or NST-ACS. Details about this protocol have been described previously by Liem et al [3]. Briefly, patients with signs and symptoms that are possibly related to a myocardial infarction are referred to a PCI center. Upon arrival, patients are immediately transferred to the catheterization department, where primary PCI of the culprit lesion is performed. Before discharge, patients are given written and oral information on the importance of medication adherence and lifestyle advices, in accordance with the European Guidelines on cardiovascular disease prevention in clinical practice [17].

After approximately 48-hours, patients are discharged from the hospital. The standard follow-up during the first year after discharge includes four outpatient clinic visits:

*Approximately 1 month after STEMI or NST-ACS*. This visit includes: a BP measurement; a 10-second, 12-lead ECG; laboratory testing (including kidney function, renal function, and lipid spectrum); and an interview with a doctor or nurse practitioner.*Approximately 3 months after STEMI or NST-ACS*. This visit includes: a BP measurement; a 10-second, 12-lead ECG; stress echo; a 24-hour Holter ECG, and an interview with a doctor or nurse practitioner.*Approximately 6 months after STEMI or NST-ACS*. This visit includes: a BP measurement, a 10-second, 12-lead ECG; a 24-hour Holter ECG; laboratory testing (including kidney function, renal function, and lipid spectrum); a transthoracic echocardiogram (TTE); and an interview with a doctor or nurse practitioner.*Approximately 12 months after STEMI or NST-ACS*. This visit includes: a BP measurement, a 10-second, 12-lead ECG; laboratory testing (including kidney function, renal function, and lipid spectrum); a TTE; and an interview with a doctor or nurse practitioner.

Patients who are randomized to regular follow-up receive the same care as patients who do not participate in the study. A flowchart of regular follow-up is detailed in Figure 1.

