### The Box

When randomized to *The Box* (Figure 2), patients will receive a box containing a weight scale, BP monitor, activity tracker, and a wearable ECG device. Patients will receive *The Box* before discharge and will be given the same written and oral information on the importance of medication adherence and lifestyle advices as the control group, in accordance with the European Guidelines on cardiovascular disease prevention in clinical practice [17]. The necessary apps will be downloaded on the patient’s smartphone; necessary accounts will be created and the installation of the devices will be carried out by a health care professional dedicated to the project. Afterwards, patients will be given oral instructions on the usage of the devices: they will be instructed to measure BP in a sitting position after five minutes of resting. The device should be applied to the left upper arm. Patients will be instructed to rest their left forearm on a table. Furthermore, a manual explaining the usage of the wearables (described below) will be handed over with *The Box*. Instruction videos are also available on YouTube. Patients who do not own a smartphone or tablet with iOS or Android OS but are willing to participate and be randomized to *The Box* will receive a smartphone. Patients will be instructed to use their own wireless Internet access (eg, home WiFi network). No mobile data network plan will be provided with the smartphone.

Patients will be instructed to record a single lead ECG, measure BP, and record their weight daily, preferably at the same time of day. Furthermore, participants will be asked to record a single lead ECG if any symptoms of possible cardiac origin occur (as interpreted by the patient). Lastly, patients will be instructed to wear their activity tracker during the day to track their daily number of steps, and at night to track the duration and quality of sleep. Patients will be told that measurements will be checked on a daily basis and that they will be contacted in cases of predefined data irregularities. Patients will be explicitly told that they cannot rely on the devices of *The Box* in emergency situations.

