### Questionnaires

All patients, in both the intervention and control groups, will be asked to fill-in a short form health questionnaire (SF-36) [18], a patient satisfaction questionnaire [19], a medication adherence questionnaire, and an International Physical Activity Questionnaire (iPAQ; to assess the patient’s level of physical activity) [20]. These questionnaires will be used within one month after myocardial infarction, six months after myocardial infarction, and twelve months after myocardial infarction.

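### SF-36 scores are to be compared by an unadjusted t-test although a baseline SF-36 is said to be collected, and the two questionnaire schedules disagree on whether that baseline exists

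*Protocol article*

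**What the plan says.** **Analysis.** Statistical Analyses gives one method for all four questionnaires and for health care use: "Scores of questionnaires (patient satisfaction questionnaire, MMAS-8 scale, iPAQ questionnaire, and SF-36 questionnaire) and health care utilization will be compared using an independent t-test". It names no wave and no covariate. The only adjustment in that section follows the blood pressure comparison and is conditional: "Logistic regression might be done if serious imbalances of baseline variables exist, to correct for potential confounding variables". Logistic regression does not apply to a continuous SF-36 score.

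**Schedule.** Questionnaires covers the SF-36 together with the satisfaction, adherence and activity forms: "These questionnaires will be used within one month after myocardial infarction, six months after myocardial infarction, and twelve months after myocardial infarction". Economic Analysis describes the SF-36 differently: "SF-36 questionnaire, which will be administered at baseline, 1 month, 6 months, and 12 months". It also says what these scores are for: "QALYs will be calculated from utility scores from the SF-36 questionnaire".

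**Start of the intervention.** The section The Box says: "Patients will receive *The Box* before discharge". Regular Follow-Up puts discharge at about 48 hours and the first visit at about one month. Patient Population allows inclusion up to 96 hours after primary PCI.

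**Randomisation.** Study Design allocates 1:1, stratified by primary diagnosis (STEMI or NST-ACS) and by five age groups. The planned total is 200 patients.

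**The concern.** Quality of life is a secondary outcome, and the SF-36 also supplies the utilities for the QALYs. If a pre-randomisation score is collected, the standard analysis uses it as a covariate, because it usually predicts the follow-up score better than any other variable. Leaving it out causes no bias in a randomised comparison but makes the confidence interval wider than it need be. The stratification factors were presumably chosen because they were thought prognostic, and they go unused as well.

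It is also unclear whether the baseline exists. If the Questionnaires section governs, there is no baseline, only a first form at some point in the month after the infarction, when Box patients may already be using the devices. If Economic Analysis governs, there is a separate baseline and a 1-month form. An analyst who took the first-wave form as the baseline could be adjusting for a score that the intervention had already changed.

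**Working it through.** **No figure to reproduce.** The document gives no power or sample size for the questionnaires. The 200 patients were derived for the blood pressure outcome. What follows compares the schedules and then sizes the loss of precision.

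**Step 1: the SF-36 schedules side by side.**

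| Source | Baseline | First month | 6 months | 12 months | Waves |
|---|---|---|---|---|---|
| Questionnaires | not listed | any time within one month | yes | yes | 3 |
| Economic Analysis | yes | at 1 month | yes | yes | 4 |

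Both rows concern the same instrument, and they differ in the number of waves.

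**Step 2: device use at the first wave.** Read literally, the first-wave window runs from day 0 to about day 30. If The Box is handed over on day 0, 2 or 4, possible use at completion runs from 0 to 30 − 0 = 30, 30 − 2 = 28 or 30 − 4 = 26 days. A form can therefore precede hand-over or follow about four weeks of use.

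**Step 3: precision with and without the baseline.**

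Inputs:
- 100 per arm (200 patients, 1:1)
- two-sided 5% test (assumed, because the document gives alpha 0.05 without sidedness)
- baseline to follow-up correlation r = 0.5, range 0.4 to 0.7 (assumption; the document gives none)
- true difference 0.4 SD (assumption)

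Formulas (normal approximation, in SD units):
- SE = sqrt((2/100) × (1 − r²))
- power = Φ(0.4/SE − 1.96)
- equivalent patients per arm without adjustment = 100/(1 − r²)

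| r | 1 − r² | Variance saved | SE | 0.4/SE − 1.96 | Power | Equivalent n per arm |
|---|---|---|---|---|---|---|
| 0 (t-test) | 1.00 | none | 0.141 | 0.87 | 81% | 100 |
| 0.4 | 0.84 | 16% | 0.130 | 1.13 | 87% | 119 |
| 0.5 | 0.75 | 25% | 0.122 | 1.31 | 90% | 133 |
| 0.7 | 0.51 | 49% | 0.101 | 2.00 | 98% | 196 |

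**Step 4: the same result as a detectable difference.** At 80% power the t-test detects (1.96 + 0.84) × sqrt(2/100) = 0.396 SD. Multiplying by sqrt(1 − r²) gives 0.343 SD at r = 0.5 and 0.283 SD at r = 0.7. At r = 0.3, below the range used above, it is still 0.378 SD.

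The stratification factors are not in these figures. Any prognostic value they have beyond the baseline score would add to the gain.

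**The case against.** The strongest defence is that nothing here is invalid. In a 1:1 randomised trial the t-test at 6 or 12 months is an unbiased comparison. These are secondary outcomes with no power target, and the size of the gain depends on a correlation that the document does not give. All of that stands, and it limits the point to efficiency. It does not remove the point: the article commits to a named test, and the covariate is one it says is collected.

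A second defence is that a condensed article may leave the tested wave and the visit windows to a fuller plan. That is fair for the choice of wave, which is not raised here. It does not cover two sections of the same article giving different SF-36 schedules.

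A reader might also infer more than the text supports:

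- **That the first wave is pooled with, or tested like, the later ones.** Statistical Analyses names no wave, so this is not stated.
- **That early satisfaction scores dilute the effect.** This needs pooling, and it needs a first wave that carries no effect. The Patient Satisfaction section links satisfaction to daily monitoring and to patients seeing their own data, which can begin around discharge, so an early form could already show a difference.
- **That unequal completion days inflate the type I error.** Questionnaires sets the same window for both arms, and nothing in the document indicates a gap between them. Any error rate would rest on invented inputs.
- **That the baseline SF-36 is discarded.** Economic Analysis uses the SF-36 scores for QALYs. The baseline is unused only in the score comparison. For the other three questionnaires no separate baseline is stated.
- **That the first form always follows The Box and precedes the first visit.** The window also covers the time before hand-over, and that visit is only approximately at one month.

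**Conclusion.** The point holds as a matter of precision and of an inconsistent schedule, not of bias. The stated SF-36 t-test is valid at 6 and 12 months but makes no use of a baseline score that the article says is collected, nor of the stratification factors. With 100 per arm and an assumed correlation of 0.5 (0.4 to 0.7), this gives up 25% (16% to 49%) of the variance. Power at an assumed 0.4 SD is 81% where 90% (87% to 98%) was available. A weaker correlation, which is possible for a form completed within days of an infarction, would shrink the gain without reversing the conclusion.

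The Questionnaires and Economic Analysis sections cannot both describe the SF-36 schedule. Until they are reconciled, the first wave cannot be assumed to be a clean baseline, because it may come before The Box or after up to about four weeks of its use.

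**What to change.** 1. **Schedule.** Make Questionnaires and Economic Analysis agree. State that the SF-36 is completed at inclusion, before randomisation, as the baseline. If a 1-month form is kept, list it as a separate wave with the same completion window in both arms.
2. **Analysis.** In Statistical Analyses, replace the t-test for the SF-36 at 6 and 12 months with ANCOVA at each time, or a mixed model over visits. Adjust for baseline SF-36, primary diagnosis and age group, and fix these covariates in advance instead of making them depend on observed imbalance.
3. **What not to adjust for.** Do not use the completion day of a form as a covariate, because it is measured after randomisation and could be affected by arm. For the same reason, do not use a first-wave form completed after randomisation as the baseline. If no pre-randomisation SF-36 is available, adjust for the stratification factors only.

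The cost is a wording change in three sections and slightly more analysis work. If the baseline form is not already given, patients also complete one short form set in hospital. No additional patients are needed.

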In addition to daily measurements, the first and third of the four standard outpatient clinic visits will be replaced by an electronic visit, in which the patient will communicate with the doctor or nurse practitioner via a secured video connection. The content of the interview will be comparable to the content of a regular outpatient clinic visit. The same doctors and nurse practitioners will perform the regular outpatient clinic visits and the digital outpatient clinic visits. In the intervention group, the 10-second 12-lead ECG and the laboratory testing one month after the index event will not be performed. Moreover, the 10-second 12-lead ECG, the 24-hour Holter ECG, laboratory testing, and the TTE 6 months after the index event will not be performed (Figure 1).

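### Low power justifies omitting a test on MACE, but not omitting an estimate with a confidence interval

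*Protocol article*

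**What the plan says.** The Study Outcomes section states that "Secondary outcomes of this study are detailed in Textbox 3", and that textbox includes MACE with eight components, from death of any cause to ischemic stroke. The Statistical Analyses section says that MACEs will only be reported and continues: "As the study is underpowered, no statistics will be done on MACEs". It adds: "The numbers will be hypothesis-generating".

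The section on The Box sets out the change in care. In that arm "the first and third of the four standard outpatient clinic visits will be replaced by an electronic visit". Of the tests due at those visits, the section says "In the intervention group, the 10-second 12-lead ECG and the laboratory testing one month after the index event will not be performed", and then "Moreover, the 10-second 12-lead ECG, the 24-hour Holter ECG, laboratory testing, and the TTE 6 months after the index event will not be performed". The same section adds monitoring: "Patients will be instructed to record a single lead ECG, measure BP, and record their weight daily, preferably at the same time of day".

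**The concern.** The sentence on MACE is a positive rule, not a detail left for the analysis plan. An analysis plan that followed it literally could give no risk difference and no interval. The reason offered does not support a rule that wide. Low power means that a non-significant test would be uninformative, so leaving out the test is sensible. An interval serves the opposite purpose, because it displays the imprecision that the authors acknowledge.

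The outcome is worth an interval because the arms differ in scheduled care in both directions. The Box loses two face-to-face visits and the tests attached to them. It gains daily home measurements that are reviewed by staff. Fewer events and more events are both plausible. A reader deciding whether the follow-up scheme can be adopted will look at the event counts, and two similar counts from about 100 patients each can seem more reassuring than they are.

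**Working it through.** **Arm size.** The only figure from the plan that enters is the total of 200 patients with 1:1 allocation, hence 100 per arm. That total was set for the primary blood pressure outcome. It can be nearly reproduced as superiority by the stated margin of 0.07, with 95% v 75% controlled, 80% power, and a one-sided alpha of 0.05 with a continuity correction. The last two are not stated in the article and are assumed here.

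- Uncorrected: n = (1.645 + 0.842)² × (0.95×0.05 + 0.75×0.25) / (0.20 − 0.07)² = 85.97 per arm.
- Corrected: (85.97/4) × [1 + √(1 + 4/(85.97×0.13))]² = 100.77, so 101 per arm, or 202 in total.

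Nothing below depends on how 200 was reached.

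**Event rate.** The article gives no expected MACE rate and no figure for precision on MACE. Its nearest anchor, in the Clinical Effectiveness section of the Discussion, is one-year mortality reported as under 10%. I therefore assume rates from 2% to 20%, equal in both arms as observed.

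**Method.** Newcombe's interval for a difference combines the Wilson limits l and u of each arm. With equal observed proportions p, the upper limit of the difference is √[(u − p)² + (p − l)²], where

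l, u = [p + z²/2n ∓ z√(p(1−p)/n + z²/4n²)] / (1 + z²/n), with z = 1.96 and n = 100.

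**Worked case, 10 v 10 events.**

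- Denominator: 1 + 3.84/100 = 1.0384.
- Centre: (0.10 + 0.0192)/1.0384 = 0.1148.
- Half-width: 1.96 × √(0.000900 + 0.000096)/1.0384 = 0.0596.
- Wilson limits: 0.0552 to 0.1744.
- Upper limit of the difference: √(0.0744² + 0.0448²) = 0.087, or 8.7 points. The lower limit is the mirror image, −8.7.

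**Range of assumed rates, 100 per arm.**

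| Observed rate in both arms | Upper 95% limit, Newcombe (points) | Simple Wald limit (points) |
|---|---|---|
| 2% | 5.2 | 3.9 |
| 5% | 6.8 | 6.0 |
| 10% | 8.7 | 8.3 |
| 15% | 10.1 | 9.9 |
| 20% | 11.1 | 11.1 |

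With 93 per arm (7% missing, the article's own trigger for imputation), the Newcombe limits at about 5%, 10% and 15% become 7.3, 8.9 and 10.5.

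**Power, for comparison.** With 100 per arm, a two-sided 5% test against a 10% control rate has about 30% power for a 7-point excess and 51% for a 10-point excess. Against a 5% control rate the figures are 43% and 66%. The authors are right that a test would be weak.

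**The case against.** The article is candid. It says the study is underpowered for MACE, calls the numbers hypothesis-generating, and repeats in the Discussion that the trial is expected to be underpowered for mortality and that a mortality difference is not its primary objective. It claims neither safety nor non-inferiority on MACE. If events are reported by arm, a reader can work out an interval. All this stands and keeps the point small. The last argument is only partly an answer, since an interval for patients with any MACE needs the number of such patients in each arm, and counts per component do not supply it.

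Three stronger readings are tempting, and the article does not support them.

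- A reader might infer that the trial means to present bare counts as proof of safety, or that an excess of 7 to 10 points is a property of the design. The first is not claimed anywhere. The second holds only for assumed, equal rates of about 5% to 15%.
- A reader might infer that The Box simply strips out monitoring. The article states no omission from the 3-month visit (ECG, stress echo, Holter) or the 12-month visit (ECG, laboratory tests, TTE). The two replaced visits are video contacts with the same staff and comparable interview content. Daily measurements come with automated warnings, daily review and contact within 48 hours. What remains true is that regular follow-up schedules laboratory tests at 1, 6 and 12 months and a TTE at 6 and 12, so The Box has neither scheduled before 12 months.
- A reader might infer that cardiac deaths will be counted twice, because any-cause and cardiac death are listed separately. Nothing says that the components will be summed, and separate lines are no error when events are only listed.

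**Conclusion.** The point holds as a minor one about reporting. The stated reason supports omitting a hypothesis test and does not support omitting an effect estimate with a confidence interval. With 100 per arm, identical observed counts would leave an excess of roughly 5 to 11 points in The Box compatible with the data, depending on an event rate that the article does not give. A benefit of the same size would be equally compatible. Similar counts would therefore not show safety, and the plan as written provides no figure that makes this visible. The primary outcome, the sample size and the conduct of the trial are unaffected.

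**What to change.** Replace the sentence that rules out statistics on MACE with wording such as:

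> No hypothesis test will be done on MACE. For each arm, the number of patients with at least one MACE (each patient counted once) will be given, together with the risk difference and its 95% confidence interval. Counts for each component will be listed descriptively. These results will be interpreted as hypothesis-generating.

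Intervals for single components are not needed. With 100 per arm some components may have very few events, and eight wide intervals could be read as informal tests.

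The cost is one more line of analysis on data already being collected, and a wide interval in the report. No extra patients, visits or measurements are required.
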